#### 1.b. Overview

A multicenter-center Phase IIa, double-blind, randomized controlled trial of a 600 mg dose of mifepristone and placebo is being proposed to determine whether there is sufficient evidence of a signal for short-term (one and three months) efficacy in veterans with chronic PTSD to warrant a Phase III trial. For this, 90 veterans with PTSD will be randomized to either mifepristone or placebo. To determine whether there is a signal, we will use statistical selection theory (see Simon et al., 1985). The final outcome will compare the proportion of clinical responders one month after treatment under the scenario: mifepristone 600 mg/day for 7 days vs. placebo. A clear benefit of this method is that it requires a much smaller sample size than traditional hypothesis testing, resulting in a reduction of both clinical costs and adverse events; this approach is widely used for Phase II drug development and testing in the pharmaceutical industry to determine whether to pursue further clinical testing of a specific compound. Based on the outcome of this exploratory trial, we will make a determination regarding whether to pursue a larger and more definitive Phase III study of mifepristone.

The innovation of studying mifepristone is twofold. The first is the application of this glucocorticoid receptor antagonist to the treatment of PTSD, which has not been studied before. The second is the use of a short-term dosing strategy that is novel in the context of classic pharmacological treatment of mental disorders. Whereas most pharmacological treatments are recommended for long-term use, the available data suggest that short-term use of a high dose of mifepristone can have enduring effects through a re-setting of the HPA axis. Short-term or intermittent dosing strategies may be particularly appealing to veterans, as complaints regarding side effects associated with long-term pharmacotherapy are common. If the initial trials in PTSD are successful, subsequent studies could assess myriad potential clinical applications in PTSD including single or intermittent dosing as monotherapy, as an adjunctive treatment to enhance or accelerate the effects of other pharmacological treatments or psychotherapy, and for PTSD prophylaxis following traumatic stress.

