#### 4.d.1. *Randomization Methods*

The randomization scheme and associated codes will be developed by the Hines Cooperative Studies Program Coordinating Center (CSPCC). Permuted block randomization will be employed to assign patients to 600 mg mifepristone or placebo. Randomization will be stratified by study site.

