#### 4.d.2. *Randomization Procedures*

Patients determined to be eligible and willing to participate in the study will be randomly assigned to 600 mg mifepristone or placebo using a web-based randomization system with a telephone call randomization system as back-up. The clinical research assistant at the participating facility will be required to sign into this password-protected site. The clinical research assistant will enter the patient study number and will be asked to answer a few questions about eligibility in order to complete the randomization procedure. If met, the website will select the first unused entry from the pre-specified list of random treatment assignments for the particular site and then assign a randomization number, which will be used to order the double-blind treatment prescription from the study site pharmacy. The randomization lists are stored on a secure server at Hines CSP Central Study File labeled "restricted access". A copy of appropriately executed and completed consent and HIPAA authorization documents must be on file at the Hines CSPCC within 24 hours of randomization, preferably before the patient is randomized. If the internet server is down during normal business hours, the clinical research assistant can telephone the Hines CSPCC to randomize a patient.

If a participant hasn't received the study drug on the day the participant is randomized, site coordinators should make every effort to ensure the participant receives the drug within 3 days post randomization, follows the directions on how to take the drug correctly, and that no study prohibited concomitant medications are used during this period. Should the study drug assignment program be down on any business day, site coordinators will contact the Albuquerque Pharmacy Center to request an emergency manual assignment.

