All SAEs require expedited notification, which is defined as the completion and submission of the SAE form in the Cooperative Studies Program electronic data capture (eDC) system within 72 clock-hours of a site investigator's initial awareness of an SAE. The VA Cooperative Studies Program Clinical Research Pharmacy Coordinating Center (PCC) will be responsible for evaluating all AEs for patient safety concerns. SAEs that are both related to the investigative treatment and unexpected will be reported to the FDA, CSR&D Director, and site investigators after review by the Study Chair, the PCC Director, and the CSPCC Director. The Hines CSPCC will generate tabulations of all AEs and SAEs for the Data Monitoring Committee (DMC) annually or on a more frequent schedule if requested by the DMC. The PCC will provide to the Hines CSPCC safety data coded per the Medical Dictionary for Regulatory Activities (MedDRA) for the DMC reports.

Additionally, criteria for stopping enrollment for a safety pause are to be implemented. If 30% of every projected 10 participants in either dose arm report an adverse event (possibly or definitely attributed to the study drug initiated by the site investigator) at a severity level of 3 or above, or if 20% of the projected 10 participants at a severity level of grade 4 or above, or if any occurrence of a grade 5 adverse event occurs,

participant accrual to that specific dose arm is temporarily paused until review by the Medical Monitor Committee (MMC). Events are graded as follow: 1 = mild side effect, 2 = moderate side effect, 3 = severe side effect, 4 = life threatening or disabling side effect and 5 = death. The Medical Monitor Committee (MMC) will be composed of a Hines CSPCC physician ([name]), a QA/Safety Monitor ([name]), Clinical Research Pharmacist from CSPCRPCC ([name].), Psychiatrist Consultant ([name] MD), and the Study Chair ([name]) to determine the relatedness to study drug. If the MMC agrees that the adverse events are related (possibly attributed or definitely attributed) to the study drug, further review by the DMC will be required. If the adverse event is not attributable to study drug, recruitment will continue. Hines would keep track of the rates as cases are reported in as well as review the cumulative data after every 10 cases on the study drug. If the DMC is asked to review the data, their recommendation of whether the study can proceed or not will be forwarded to the Director, CSR&D, for approval.

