##### 4.n.2. *Sample size determination*

As mentioned above, the sample size has been calculated to provide at least 90% probability that mifepristone 600 mg has been correctly identified as being superior to placebo if the population difference in response rate is at least 15%. Using the calculations provided by Simon et al. (1985) and accounting for a 20% attrition rate which has been reported in other drug studies using a similar population (Bartzokis et al., 2005), a total sample size of 90 is required, or 45 per treatment group. Since the sample size varies according to the responder rate (as well as the magnitude of the difference of interest), and the responder rate for placebo is unknown, we assume a placebo responder rate of 40%, which is at the high end of the studies referenced above. By contrast, in order to have a one-sided Type I error rate of 5% and 80% power to detect the 15% difference between two

groups using a traditional hypothesis testing framework, the study would require 274~344 participants when the placebo responder rate changes from 20% to 44%, after adjustment for a 20% withdrawal rate. If the true population difference in response rate is smaller than 15% (between 10~12%) and if we still consider it clinical significant, the proposed sample size (n=72 completers or 90 with 20% withdrawal rate) will still provide at least 80~85% probability of correctly identifying the superior group.

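### The safety rule pauses accrual to one arm of a two-arm blinded trial; it should pause randomization to the whole trial

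*Protocol*

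**What the plan says.** Protocol section 4.i (Safety Monitoring) introduces the rule by saying that "criteria for stopping enrollment for a safety pause are to be implemented". For every 10 participants in either arm, it fires if 30% have a drug-attributed adverse event of grade 3 or above, or if 20% have one of grade 4 or above. Any grade 5 event also fires it. The action is then: "participant accrual to that specific dose arm is temporarily paused until review by the Medical Monitor Committee (MMC".

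The rest of the paragraph is worded for the trial as a whole. After the committee's review, "If the adverse event is not attributable to study drug, recruitment will continue". If the data monitoring committee is consulted, "their recommendation of whether the study can proceed or not will be forwarded" to the research service's director.

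The design is given elsewhere in the protocol:

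- Section 1.b: a "double-blind, randomized controlled trial of a 600 mg dose of mifepristone and placebo is being proposed".
- Section 4.d.1: "Permuted block randomization will be employed to assign patients to 600 mg mifepristone or placebo", stratified by site.
- Section 4.d.2: "the website will select the first unused entry from the pre-specified list of random treatment assignments for the particular site".
- Section 4.n.2: "a total sample size of 90 is required, or 45 per treatment group".

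**The concern.** An arm-specific pause can work where several doses are studied, because new participants can still be randomized among the arms left open. Here there is one active dose and placebo. If mifepristone triggers the rule, every new enrollee gets placebo. If placebo triggers it, every new enrollee gets mifepristone while a safety review is open. In both cases randomization stops while enrolment goes on.

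Three things are at stake:

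- Participants enrolled during a pause have no concurrent control, although the primary analysis (section 4.p.1) compares the two groups' responder rates directly.
- The clause needs an assignment procedure that section 4.d.2 does not contain.
- Anyone who learned which arm was paused would know what new participants receive. The protocol does not say that anyone would be told, so this risk is conditional.

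This is the only sentence in the protocol that says what happens when the rule fires, and it has to be acted on at once.

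**Working it through.** **Can the clause be carried out on the stated system?** Each site has one fixed permuted-block list, and the website issues the next unused entry. With one arm closed there are two possibilities:

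1. *Skip* the closed arm's entries. Enrolment continues, all of it to the other arm, and the blocks are broken.
2. *Stall* any site whose next entry belongs to the closed arm. The list order survives, but a stalled site reveals its next assignment, and the sites that go on enrolling do so only to the open arm.

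Either way, a participant enrolled during the pause receives the open treatment with probability 1 instead of 1/2.

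**How many participants?** Inputs are from the Recruitment and Feasibility section: three main sites at 0.8 per month each, and two added sites at 0.5 to 0.6 per month each over 9 to 10 months.

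- Main sites only: 3 × 0.8 = 2.4 per month.
- With the added sites: 2.4 + 2 × 0.5 = 3.4, up to 2.4 + 2 × 0.6 = 3.6 per month.
- Share of the trial per month of pause: 2.4/90 = 2.7%, up to 3.6/90 = 4.0%.
- Number who would otherwise have gone to the paused arm under equal allocation: 2.4/2 = 1.2, up to 3.6/2 = 1.8 per month. This is 1.2/45 = 2.7% to 1.8/45 = 4.0% of a planned group.

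The protocol gives no pause length. For an assumed 1 month, 2.4 to 3.6 participants go to one arm. For an assumed 3 months, 7.2 to 10.8 do. These counts describe skipping with recruitment at its planned pace; stalling would give fewer.

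**How likely is a trigger?** The protocol gives no event rates. For assumed true rates of attributable grade 3 or higher events, the binomial probability of 3 or more among 10 participants is:

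| Assumed rate | P(3 or more of 10) |
|---|---|
| 5% | 0.012 |
| 10% | 0.07 |
| 15% | 0.18 |
| 20% | 0.32 |

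These apply to one group of ten and to the first criterion only.

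**Is the sample size affected?** The plan's figure reproduces. With 36 completers per group and responder rates of 55% and 40%, the probability of correct selection is 0.899 (exact, ties split evenly) or 0.901 (normal approximation), and 72/(1 − 0.20) = 90.

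Now take 11 participants enrolled to one arm during an assumed 3-month pause. About 11 × 0.8 ≈ 9 complete. The other 72 − 9 = 63 completers split 31 and 32, giving 31 versus 41. The probability of correct selection is then 0.898, so the imbalance itself costs almost nothing.

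**The case against.** The strongest reply is that the intent was trial-wide. The lead-in, the resumption sentence and the final recommendation all refer to enrolment or the study without naming an arm. A full halt is also the only pause that sections 4.d.1 and 4.d.2 can deliver as written. On this view one-arm enrolment would not follow from the protocol, because someone would first have to build a way of skipping entries, and the clause is a slip of wording. The Operations Manual, which is not shown, may hold the procedure. Adverse events are counted centrally, and nothing says sites would learn which arm triggered. A pause might be short, a trigger may be unlikely, and the section on the treatment algorithm (4.e) expects no study-related serious adverse events.

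Much of this stands. The intent probably was trial-wide, the blinding risk is only conditional, the counts depend on a literal arm-only pause, and the decision rule is barely touched. It does not rescue the clause. The surrounding sentences never say that the other arm closes too, and the one sentence that names the action says something different. An operations manual should carry out the protocol's rule, not reverse it. The likely intent is a reason to correct the wording.

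**Conclusion.** The concern holds. The clause is wrong as written: followed literally, it replaces randomization with certain assignment to one treatment for everyone enrolled during a pause, and it conflicts with the trial-level wording around it.

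The effect is confined to those participants. It is at most 2.4 to 3.6 per month of pause, assuming planned accrual continues and the paused arm's entries are skipped. The total cannot be given, because the length and frequency of pauses are not stated. There is no case for changing the sample size. The correction is worth making because this is an executable safety instruction in a blinded trial, and staff should not have to override its wording to do the right thing.

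**What to change.** In section 4.i, replace the arm-specific clause with wording such as: *randomization to both groups at all sites is suspended pending MMC review*. Keep the thresholds and the central counting by treatment group as they are. Add that the notice of a pause must not name the group that triggered it.

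The change is one clause plus that addition. During a pause nobody is randomized, so the site blocks and the 1:1 allocation stay intact. The price is delay: about 2.4 to 3.6 enrolments deferred per month of pause at the planned rates.

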The study DMC will be the CSR&D Psychiatric, Behavioral Health & Neurologic Disorders Central Data Monitoring Committee. The cDMC will initially meet before or at study start-up, determining at the first meeting the frequency of progress reviews required for the study, but will meet no less than annually. The cDMC will review the progress of the study including patient intake, completeness of follow-up, data quality, protocol deviations, and safety, and will also review any protocol modifications recommended by the EC. The cDMC will intermittently review data provided by study statisticians. The cDMC will make recommendations to the Director, CSR&D, through the Director, Hines CSPCC, as to whether the study should continue, be placed on probation, or be terminated.

The Study Group, which consists of all participating investigators and site clinical research assistants and assistants, will meet annually to discuss the progress of the study and any problems encountered during the conduct of the trial. Study personnel will adhere to ORD policy on human subjects' protections by fully completing approved Good Clinical Practices (GCP) training per VHA Handbook 1200.05. Completed training certificates will be provided by personnel to Hines Coordinating Center to maintain on file throughout the study. SMART (Site Monitoring, Auditing, and Resource Team), a division of the CSP Clinical Research Pharmacy Coordinating Center (CSPCRPCC), may conduct a full audit of participating sites if requested by the sponsor (CSR&D). The study will be monitored utilizing centralized data and statistical monitoring methods and remote-based source verification; which will be based on risk assessment and management strategies.

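### A safety pause triggered by an arm's event rate or a death can be lifted on a relatedness judgement, and the DMC must look only if the events are judged at least possibly related

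*Protocol*

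**What the plan says.** Protocol 4.i (Safety Monitoring) sets three triggers. The first is worded "If 30% of every projected 10 participants in either dose arm report an adverse event (possibly or definitely attributed to the study drug initiated by"; its remaining words name the investigator at that centre and set the severity at grade 3 or higher. The other two are worded "if 20% of the projected 10 participants at a severity level of grade 4 or above, or if any occurrence of a grade 5 adverse"; the last of these means any death. On a trigger, "participant accrual to that specific dose arm is temporarily paused until review by the Medical Monitor Committee (MMC").

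The MMC consists of a coordinating-centre physician, a QA/safety monitor, a clinical research pharmacist, a psychiatrist consultant "and the Study Chair ([name]) to determine the relatedness to study drug". If it finds the events possibly or definitely attributable, "further review by the DMC will be required". If it does not, "If the adverse event is not attributable to study drug, recruitment will continue".

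Section 4.i also has the coordinating centre follow the rates as reports arrive and look at the cumulative data after each 10 cases on study drug. Outside the pause route, AE and SAE tabulations are prepared "for the Data Monitoring Committee (DMC) annually or on a more frequent schedule if requested by the DMC". Under 4.l.1 the central DMC fixes its review frequency at its first meeting "but will meet no less than annually". Section 4.p.1 (Secondary Outcomes, item 2) adds faster safety reporting for each two adverse events in ten participants, but names no recipient and no action.

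**The concern.** The trigger and the release test ask different questions. Two of the three triggers are event rates in an arm. The release test is whether the events are attributable to the drug. Judging causality in individual cases does not show whether one arm has more severe events than the other; that takes counts by arm. The MMC is given no task of comparing arms. The DMC, which under 4.l.1 recommends whether the study continues, sees a trigger through this route only if the MMC agrees on relatedness.

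The gap matters most where the disease itself offers an explanation. Section 1.a associates PTSD with higher mortality from suicide and cardiovascular disease, so a death could reasonably be judged unrelated when taken alone. It would then not reach the DMC by this route. What is at stake is continued enrolment after a crossed threshold, without the comparison that would show whether the threshold reflects the drug.

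**Working it through.** The protocol gives no operating figure for the pause rule, so there is none to reproduce. The check has three steps.

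**1. Does any sentence send a released trigger to the DMC?**
- MMC finds the events at least possibly related: DMC review is required (4.i).
- MMC finds them unrelated: recruitment continues (4.i), and no DMC notice is mentioned.
- Coordinating-centre rate tracking and the review after every 10 cases (4.i): no referral is attached.
- Accelerated reporting (4.p.1): no recipient or action is given.
- Local IRB review of SAEs (4.l.1): no counts by arm are mentioned.

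So after a release, the next DMC look that the text assures is the scheduled one, at most a year away.

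**2. How many could be randomized in that year?** The inputs are the site rates in the Recruitment and Feasibility section and the total of 90 in 4.n.2.
- Three main sites: 3 × 0.8 = 2.4 per month; × 12 = 28.8, which is 32% of 90.
- Plus two added sites at 0.5: 2.4 + 1.0 = 3.4 per month; × 12 = 40.8, or 45%.
- Plus two added sites at 0.6: 2.4 + 1.2 = 3.6 per month; × 12 = 43.2, or 48%.

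The range is about 29 to 43 in total, or about 14 to 22 per arm. The upper end runs the five-site rate for a full year. The added sites are planned for only 9 to 10 months at 5 to 6 participants each, so a year containing that whole period gives 28.8 + 10 to 12 = about 39 to 41. Treatment lasts seven days (4.e), so nearly all of these participants would have finished dosing by then.

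**3. Would the pause trigger again?** The rule applies to each 10 participants, so 14 to 22 more in an arm complete one or two further blocks. The chance that a block of 10 reaches 3 or more, P(X ≥ 3) with X ~ Binomial(10, p), where p is an assumed true rate of site-attributed events of grade 3 or above (the documents give none), is:

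| p | one block | two blocks, 1 − (1 − P)² |
|---|---|---|
| 10% | 0.07 | 0.14 |
| 20% | 0.32 | 0.54 |
| 30% | 0.62 | 0.85 |

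A large persisting excess would thus probably trigger again within two blocks, and a moderate one about half the time. Each new trigger meets the same relatedness gate, so triggering again does not by itself bring in the DMC.

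**The case against.** Triage by a medical monitoring committee with conditional escalation is a coherent structure, and the protocol does not contradict itself here. The bar for referral is low: a finding of possibly attributed is enough. Releasing a grade 3 trigger means overruling the site's attribution for enough events to bring the count below the threshold. The coordinating centre follows the rates separately, the pharmacy coordinating centre evaluates all AEs, and the DMC may ask for tabulations at any time. The DMC charter and any MMC procedures are not shown. All of this stands, and it limits the size of the gap. None of it creates a referral when the MMC says no.

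A reader might infer more than the text supports:
- *The MMC can only downgrade the site's attribution.* Not for a death. The grade 5 trigger carries no site-attribution condition, and the grade 4 clause does not repeat it. The MMC could find related a death that the site called unrelated, and DMC review would then be required.
- *The arms are never examined independently of the MMC.* The gap concerns the decision to resume accrual. Scheduled and requested DMC tabulations continue.
- *The Study Chair controls the restart.* The Chair is one of five members, and no voting rule is stated.
- *The MMC will unblind itself to judge relatedness.* Nothing says so. Section 4.j.1 limits unblinding to what the care of a medical complication requires.

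**Conclusion.** The point holds as a gap in the escalation route. A pause triggered by a rate or a death can be lifted on relatedness alone, without the DMC seeing counts by arm before its next scheduled review. The figure of 29 to 43 participants (32% to 48% of the trial) is an upper bound, not an expected exposure. It assumes that the release falls just after a DMC review, that the DMC keeps to the annual minimum, that it asks for nothing sooner, and that no later block triggers a pause leading to referral. No sample size, error rate or analysis is affected. The case for change rests on better safety oversight at little cost, not on an error in the plan's figures.

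**What to change.** In 4.i, have the coordinating centre send every triggered pause promptly to the central DMC, for review by its chair or ad hoc, with event counts by arm. The MMC's blinded relatedness assessment should accompany that referral instead of deciding whether it is made, and accrual should resume after the DMC responds. The trigger thresholds and the MMC's membership need not change.

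The cost is a revised paragraph in 4.i and, if needed, a matching line in the DMC charter. The DMC already exists, and the coordinating centre already tracks the rates and holds the randomization lists (4.d.2), so no new body or data flow is needed. The downside is that a pause may last somewhat longer when the events prove unrelated.
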